#### **7.3.4. Meningitis**

In Grady's series of 513 patients, one patient reportedly developed meningitis (0.2% incidence) but this was attributed to the transsphenoidal hypophysectomy that the patient had undergone [30]. Cheung and colleagues described two patients out of 162 (1.2%) who developed meningitis after having CSF drainage during thoracoabdominal aortic repairs; one who developed it after the drain was removed, and the other whose catheter fractured off [36]. Coplin and colleagues reviewed 312 patients undergoing lumbar CSF drainage and found an infection rate of 4.2% (13 of 312) [37]. Two-thirds of these patients had already undergone previous CSF drainage procedures or had persistent CSF fistulae, implying that their risk of infection was already higher with a previously "exposed" CSF space. All lumbar drain infections were treated successfully with antibiotic therapy and without neurological deficit. The lumbar intrathecal catheter will remain in situ for up to 7 days for the purpose of intrathecal pressure and spinal cord perfusion pressure monitoring and collection of CSF samples every 8 hours. It is not unreasonable to expect a lower infection rate in SCI patients that have neither CSF fistulae nor a previous drainage procedure. ***The estimated risk of meningitis due to insertion and presence of the lumbar intrathecal catheter is therefore approximately 1%.***

Clinical surveillance of the CSF will be done as per the institutional protocols. At Vancouver General Hospital, a 1 ml sample of CSF is sent daily to the lab for gram stain, cell count, and bacterial culture. We know that the injury itself will induce some meningeal inflammation and elevate the cell count and protein levels; in this regard, the gram stain and bacterial culture will be the critical components of this evaluation. In addition, vital signs of patients will be continuously monitored by nursing staff. A fever of  $\geq 38.5^{\circ}\text{C}$  within 24 hours of a positive CSF culture and in the absence of other concurrent infection will be considered to be supportive of the diagnosis of meningitis. If meningitis becomes evident (positive bacterial culture, positive gram stain, and an associated fever of  $\geq 38.5^{\circ}\text{C}$ ), it is expected that the patient will be started on the appropriate antibiotics and the lumbar intrathecal catheter discontinued.

### 7.3.5. Additional Note on AEs Related to Intrathecal Catheters

The AEs we are particularly concerned with are those that are related to the intrathecal catheters (post-dural puncture headache with associated nausea and vomiting secondary to CSF leakage, neurologic injury due to the insertion of the drain, and meningitis). **In our CAMPER study we did not experience these complications.** In particular, on the issue of meningitis, the risk of this AE would presumably increase the longer that it is left in situ. Catheters were in place for up to 5 days, and no infectious complications related to the catheter occurred. We feel that increasing the time in which the catheter is inserted to 7 days is reasonable, based on our previous 5 day data and on our clinical experience at the Acute Spine Unit at VGH of not having infectious complications with these catheters when they are in place for less than a week. Nonetheless, we will be monitoring the catheters very closely both clinically and with standard CSF measurements to look for signs of meningitis.

## 8. Biochemical Outcomes & Long Term Storage

### 8.1. Central Laboratory & Long Term Storage in the International Spinal Cord Injury Biobank (ISCIB)

All CSF and serum samples collected will be sent to, and stored at, a central laboratory facility under the direction of [name] at the Blusson Spinal Cord Centre in Vancouver. Full central laboratory contact information and shipping procedures are detailed in the CASPER study manual. Samples will be stored at -80°C in temperature-monitored freezers.

Access to CASPER study freezers is strictly controlled with only authorized CASPER study laboratory personnel having access to study samples. Study samples will be labelled with only the participant's unique study identification number. No personal identifiable information is included on the sample label.

All study samples will be kept until all analyses (as per the study protocol) and publication/presentation of such analysis is completed. After this time, remnant biospecimens (and their corresponding demographic and injury related data) will be stored indefinitely within the **International Spinal Cord Injury Biobank (ISCIB)** and used for future studies under the governance of ISCIB.

### 8.2. CSF Biomarkers for Injury Stratification and Prediction of Outcome

Based on past work, the CASPER trial will utilize CSF biomarkers to help in the stratification and prediction of outcome. The CSF will be obtained at ~24 hours post-injury from the intrathecal catheter that is installed as part of the hemodynamic management of the patient.

The CSF biomarkers that will be specifically targeted include: IL-6, IL-8, MCP-1, GFAP, S100 $\beta$ , and tau. CSF will be analyzed using a Meso Scale (Meso Scale Discovery, Rockville, MD) multiplex electrochemiluminescent antibody detection assay for IL-6, IL-8, TNF-R1, MCP-1, and IP-10, using a custom 5-plex kit (K15067M, F210V). Plates will be read on the QuickPlex SQ 120 (Meso Scale Discovery), and the data will be analyzed using MSD Discovery Workbench software.

CSF levels of total tau (T-TAU; KHB0042, Invitrogen), S100 $\beta$  (RD192090100R; Biovendor, Modrice, Czech Republic) and GFAP (RD192072200R; Biovendor) will be determined using specific commercially available enzyme-linked immunosorbent assay (ELISA) kits. For each of these individual ELISAs, the assay sensitivities for tau, S100 $\beta$ , and GFAP are 10pg/mL, 15pg/mL, and 45pg/mL, respectively. The intra-assay coefficients of variation (CV) have been less than 5.9, 3.8, and 6.4%, and inter-assay CVs have been less than 9.0, 10.1, and 6.1 for tau, S100 $\beta$ , and GFAP respectively. Concentration levels of these structural proteins were determined based on a standard curve generated on each plate using manufacturer-supplied reagents. For each analyte,

samples have been assayed in duplicate and average concentrations were used for statistical analysis.

Additional biomarker studies for UCH-L1, GFAP, and NF-L will be conducted on CSF and serum using a Quanterix Simoa HD-1 (<https://www.quanterix.com/products-technology/instruments/hd-1>), a fully automated analyzer with the ability to perform a digital ELISA. Simoa improves detection over conventional immunoassays by 1000-3000X by isolating individual capture beads in femtoliter-sized reaction wells [38]. Because array volumes are 2 billion times smaller than conventional assays, only a single molecule is needed to reach the detection limit. This increases the potential of establishing serum biomarkers. This biomarker work will be conducted in collaboration with [name], Department of Pathology and Laboratory Medicine, The University of British Columbia. [name] is one of the first in Canada to operationalize a Quanterix Simoa in her lab, and is currently collaborating with [name] in evaluating these biomarkers on this extremely sensitive platform.

### **8.3. Biospecimen Storage within ISCIB**

CSF and blood samples will be utilized for the biomarker analyses as described above. CSF and blood biospecimens not used in the immediate biomarker analysis will be stored within ISCIB for future analysis. As part of CASPER participation, patients will also be consenting to the long-term storage and secondary analyses of their biospecimens within ISCIB. ISCIB was established by [name] who currently is the Director of the Biobank.

**ISCIB Mission:** The MISSION of the Biobank is to advance the understanding of the biology of SCI through the study of human biospecimens.

**ISCIB Vision:** The VISION of the Biobank is that it will serve as a resource to the global SCI research community. It is expected that the Biobank would be accessed by investigators from around the world to address research questions about the biology of human SCI that previously may have only been investigated in animal models. It is envisioned that insights into the biology of human SCI, derived from the investigation of biobank specimens, will help to inform the translation of scientific discoveries from “bench to bedside”. Further, such insights will be utilized in a “bedside back to bench” manner to guide subsequent scientific studies in animal models.

**ISCIB Objectives:** The OBJECTIVE of the Biobank is to support research into the biological responses of human SCI. To do this, the Biobank will share biospecimens with requesting investigators who have established research protocols for biospecimen evaluation.

## International Spinal Cord Injury Biobank Governance Structure

[figure not shown]

### A. ISCIB Executive Advisory Committee (EAC)

The EAC is responsible for the oversight, strategic direction, and overall function of ISCIB. The roles of the EAC include:

- Finalizing and approving the annual report, including the budget.
- Advising strategic direction and priorities.
- Providing guidance around long-term financial sustainability.
- Advocating with the public.
- Maintaining the transparency and ethical nature of biobank operations.
- Assisting the ISCIB Director with decision-making as required.

### B. ISCIB Operational and Scientific Access Committee (OSAC)

The OSAC is responsible for the management and operations of the Biobank. Importantly, the OSAC is responsible for decision-making around the usage of biospecimens within the bank. The roles of the OSAC include:

- Establishing and recommending the annual budget.
- Providing oversight and input around the priorities for collection, storage, quantity, quality, and nature of biospecimens.
- Ensuring that the biobank operates according to its declared standards.
- Reviewing requests for biospecimens and deciding upon their distribution in accordance to the mission and vision of ISCIB.
- Reviewing inventory and availability of biospecimens relative to demand.
- Establishing research priorities for access to biospecimens.

## 9. DATA COLLECTION AND DATA MANAGEMENT

Data collection at each participating study site will be assisted by the use of CASPER study case report forms (CRFs). All data about the participant that is stored at each participating study site, such as CRFs will be coded with a study ID only instead of their name. The documents (electronic or paper) linking the participant's name to the CASPER ID number (e.g., enrollment log, ICF, contact information forms) are only accessible by the local CASPER site research team.

De-identified study data will then be entered into the Global Research Platform (GRP). The GRP is a state-of-the-art, web-based, secure data collection, storage and research management system developed and operated by the Praxis Spinal Cord Institute, formerly the Rick Hansen Institute. The GRP is highly flexible and adaptable, and can be used to run multiple concurrent registries and studies, from local institution clinical data gathering to multicentre clinical trials. GRP is hosted in a top-tier secure data centre in Canada, and meets global privacy and security standards. The GRP is also 21 CFR Part 11 compliant.

User access to data is controlled by study role (i.e. Research Coordinator, Study Manager, Study Monitor, Principal Investigator), the study and the facility to which the user belongs. To access the GRP, the user requires a valid username and password, and a certificate installed on the user's computer that expires and needs to be renewed annually. The certificate is issued when a valid user account has been created.

As a multicenter study, participating CASPER study sites will only see data entered from their own study site. As the principal investigator, [name] at the University of British Columbia and his delegated research team members will have access to the de-identified study data provided by all of the participating study sites.

CASPER data will be analyzed as described in the protocol and only de-identified data will be included in reports and publications.

## 10. EFFICACY ENDPOINT

The primary purpose of the CASPER trial is to determine if active management of SCPP results in improved neurologic recovery at 6 months post-injury as compared to conventional hemodynamic management.

Neurologic recovery will be measured using the ISNCSCI examination. Our primary outcome measure will be the change in total motor score at 6 months post-injury (a time point at which most motor recovery has occurred and is commonly used in acute SCI clinical trials). To assess whether active SCPP management (SCPP  $\geq$  65 mmHg x 7 days) promotes better neurologic recovery than conventional MAP management, our **control group will be the prospectively collected (and conventionally managed) cohort from our CAMPER study**. The major

advantage of this CAMPER cohort is that it represents a well-documented & prospectively collected set of neurologic, hemodynamic, and biomarker data.

### **Sample Size Calculation.**

The most conventional approaches to establishing sample size consider either AIS grade conversion or motor score improvement. Here, we have considered both AIS grade conversion and motor score improvement. If we were to consider “AIS Grade Conversion” to be our primary outcome measure, and address the question of whether active SCPP management promoted AIS grade improvement as compared to conventional MAP management, then using the clinical grading alone, a 10% improvement would require an  $n=143$  for 80% power, based upon our previous publication in which we evaluated AIS grade improvement as predicted by either the baseline AIS grade, MRI, or CSF biomarkers [20]. However, if using the CSF biomarkers to predict outcome, a 10% improvement would require an  $n=72$  for 80% power. Because we recognize that the CSF biomarkers will help in predicting outcome, but that the strength of this prediction will likely be less in a completely independent cohort of patients, we do not feel that reducing the sample size nearly in half (from 143 to 72) is prudent. Hence, we propose an  **$n=100$** , assuming a more conservative improvement in our ability to predict outcome with the CSF biomarkers.

Secondarily, if we view a 7-point improvement in motor score as both clinically meaningful/achievable, then we require the enrolment of  $\sim 74$  cervical SCI patients into this proposed study, based upon a standard deviation of 11 points, reflecting  $\alpha=0.0499$  and  $\beta=0.806$ . A 7-point motor score change is chosen because this “effect size” is what appears to be achievable with early surgical decompression in acute SCI [39, 40]. Assuming that we will also include thoracic SCI where motor score improvement is not as responsive due to the inability to assess segmental motor recovery, we feel that enrolling a total of 100 patients would be more sufficient in this study.

**Analysis Plan.** We will use multivariable linear and logistic regression to model the association between the intervention (SCPP management vs. MAP management) and neurologic outcome (motor score improvement or rate of AIS grade improvement). Anticipated co-variables to control for include AIS grade, neurologic level, baseline motor score, 24 hr post-injury CSF biomarker levels, age, and gender. As a sensitivity analysis we will utilize propensity score matching, a statistical approach that we have employed previously in an assessment of methylprednisolone for acute SCI [41].

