## 2.4. The Canadian Multicenter CSF Pressure and Biomarker Study (CAMPER)

Following the findings of our small prospective randomized clinical trial on CSF drainage, a decision was made to make the study a prospective observational trial whereby we inserted the lumbar intrathecal catheters but only observed ITP and SCPP (rather than actively draining CSF to reduce ITP). This protocol was initiated locally at Vancouver General Hospital, and then expanded to four other hospitals in: London, Ontario; Halifax, Nova Scotia; Montreal, Quebec; and San Francisco, California.

Inclusion criteria included: cervical or thoracic SCI, admitted within 48 hours of injury, and the ability to obtain a neurologic assessment and informed consent (thus excluding those with head injuries or multi-trauma). The CAMPER protocol involved the insertion of a lumbar intrathecal catheter and the monitoring of ITP for 5 days. No active measures were conducted to change the ITP by draining CSF. CSF and blood samples were obtained approximately 3 times per day for biomarker studies.

In 2017 we reported on the ITP, SCPP, and MAP data and how this related to neurologic outcome. This cohort included 91 patients: 72 males, 19 females, 54 cervical, 37 thoracolumbar, and 57 AIS A, 17 AIS B, and 17 AIS C for whom we had 6 month follow-up data [11].

Firstly, we mapped out every recorded MAP, ITP (or CSF Pressure, “CSFP”), and SCPP for every patient throughout the entire period of time they had the lumbar drain in ([Figure 3](#)).

**Figure 3.** MAP, CSFP, and SCPP over 5 days in all patients.

[figure not shown]

Then, we examined neurologic outcome with respect to AIS grade conversion at 6 months post-injury. We looked at every single recorded MAP, ITP, and SCPP, and examined whether each of these data points was related to AIS grade conversion, or no conversion. This enabled us to generate “transition points” at which point the chance of AIS Grade conversion versus the chance of no AIS Grade conversion was EQUAL (i.e. The ‘relative risk’ of not improving versus improving an AIS grade was 1.0). For MAP, CSFP, and SCPP these transitions points occurred at 70, 29, and 50 mmHg, respectively (**Figure 4**).

**Figure 4.** Relative risk of not improving an AIS grade. Here, one can appreciate that the relative risk of not improving an AIS grade increases as the MAP and SCPP decreases, and as the CSFP increases.

[figure not shown]

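### The AIS-conversion justification for n=100 claims 80% power for a 10% improvement without visible allowance for the roughly 91 CAMPER controls; against them power is about 28-35% unadjusted and 38-61% with the assumed biomarker gain

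*Protocol*

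**What the plan says.** Section 10 (Efficacy Endpoint) names the primary outcome: "Our primary outcome measure will be the change in total motor score at 6 months post-injury". It also names the comparator: the "control group will be the prospectively collected (and conventionally managed) cohort from our CAMPER study". Section 2.4 gives the size of that cohort with six-month follow-up: "This cohort included 91 patients: 72 males, 19 females, 54 cervical, 37 thoracolumbar".

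The Sample Size Calculation in Section 10 considers AIS conversion first, as a hypothetical primary outcome, "and address the question of whether active SCPP management promoted AIS grade improvement as compared to conventional MAP management". It states that "using the clinical grading alone, a 10% improvement would require an" n of 143 "for 80% power, based upon our previous publication in which we evaluated AIS grade improvement", and that using the CSF biomarkers would bring this down to 72. It then says "we do not feel that reducing the sample size nearly in half (from 143 to 72) is prudent" and proposes 100, on the ground that biomarker prediction will be weaker in an independent cohort. A motor score calculation (7 points, SD 11, about 74 cervical patients) follows as a secondary argument for the same total.

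The Analysis Plan in Section 10 is a two-group model: "We will use multivariable linear and logistic regression to model the association between the intervention (SCPP management vs. MAP management) and neurologic outcome", with AIS grade, neurologic level, baseline motor score, 24-hour CSF biomarkers, age and gender as covariates.

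For the AIS figures the protocol states no control rate, alpha, sidedness, formula or control-group size, and does not say whether the 10% is absolute or relative.

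**The concern.** The comparison is between two samples, and one of them is already closed at about 91. Its conversion rate is an estimate whose uncertainty enters the treatment contrast alongside that of the new patients. A required n of 143 for a 10-point difference is far below what a two-sample comparison needs at ordinary conversion rates, and the AIS paragraph does not mention the number of controls.

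AIS conversion is named with motor score in the first Specific Aim (Section 1), is a modelled outcome in the Analysis Plan, and gives the first derivation of the total of 100. A reader would conclude that 100 patients give about 80% power for a 10% improvement in conversion. A null AIS result could then be taken as evidence against SCPP management, although the comparison had well under that chance of detecting such a difference.

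**Working it through.** **Inputs from the protocol:** 100 new patients (Section 1), 91 controls (Section 2.4), 10% improvement, 80% power, and n of 143 / 72 / 100 (Section 10).

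**Assumptions:** two-sided alpha 0.05; an absolute gain of 10 points; control conversion p0 of 20%, 30% or 40%; all 100 new patients evaluable at six months. The protocol gives no CAMPER conversion rate. The only conversion rates it cites are 37.0% and 43.2%, for AIS A patients in another cervical study (Section 2.5). Reading the 10% as relative does not help: even a test against a fixed rate would then need 175 or more patients at base rates of 20-80%.

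**1. Reproducing 143.** With no base rate stated, it can only be back-solved.

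- Test against a fixed rate: n = [1.96·√(p0q0) + 0.842·√(p1q1)]² / 0.10². At p0 = 0.21, p1 = 0.31: (1.96×0.407 + 0.842×0.462)² / 0.01 ≈ 141. At 20% it is 137 and at 22% it is 145. One-sided (1.645 in place of 1.96), it is 136 at 30% and 145 at 35%.
- Two-sample, per group: n = [1.96·√(2p̄q̄) + 0.842·√(p0q0 + p1q1)]² / 0.10². At 30% versus 40%: (1.96×0.675 + 0.842×0.671)² / 0.01 ≈ 356. At 20% it is 294 and at 40% it is 388.
- A two-sample design gives 143 per group only at base rates near 5% or 85% (two-sided), or 8% or 82% (one-sided).

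**2. Power of 100 versus 91 for +10 points, unadjusted.** Power = Φ[(0.10 − 1.96·SE0) / SE1]. Worked at p0 = 0.30:

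- pooled rate = (100×0.40 + 91×0.30)/191 = 0.352
- SE0 = √[0.352×0.648×(1/100 + 1/91)] = 0.0692
- SE1 = √[0.40×0.60/100 + 0.30×0.70/91] = 0.0686
- (0.10 − 0.1357)/0.0686 = −0.52, so power = 0.30

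**3. Allowing for the biomarker gain.** Both group sizes are divided by a variance factor taken from the protocol's own ratios: 100/143 = 0.70 (the gain behind n=100) or 72/143 = 0.50 (the gain it declines to rely on in full). Effective sizes become about 143 versus 130, or 199 versus 181. This scaling is an approximation.

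| Precision gain | Power for +10 points at p0 = 20 / 30 / 40% | Detectable difference at 80% power (points) |
|---|---|---|
| None | 35 / 30 / 28% | 18.4 / 19.8 / 20.2 |
| 100/143 | 48 / 41 / 38% | 15.1 / 16.4 / 16.9 |
| 72/143 | 61 / 53 / 50% | 12.7 / 13.9 / 14.3 |

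**4. Sensitivity.** One-sided at 5%, power is 40-48% unadjusted, 50-60% with the 100/143 gain and 62-73% with the full gain. Enrolling 143 new patients against the same 91 gives 32-39% (two-sided, unadjusted).

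**5. Declared primary endpoint.** With 7 points, SD 11, 74 new cervical and 54 CAMPER cervical patients: SE = 11·√(1/74 + 1/54) = 1.97, 7/1.97 = 3.56, and power = Φ(3.56 − 1.96) ≈ 0.94.

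**The case against.** The strongest reply has three parts.

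- **AIS conversion is not the primary outcome.** The protocol introduces it conditionally, and 100 has a second justification through motor score. This stands. A reader might infer that the trial as a whole is underpowered, but on the protocol's own motor inputs the cervical comparison has about 94% power.
- **The planned analysis is adjusted, and n=100 rests on a biomarker gain.** This also stands. It would be tempting to quote 28-35% as the trial's power, or to say that only an 18-20 point difference could be seen. Those are unadjusted figures, and the adjusted rows of the table must sit beside them. It would be equally tempting to say that no enrolment could reach 80%. Without adjustment, unlimited new patients against 91 controls do stop at 48-56%. The ceiling rises to 63-73% with the 100/143 gain and 77-87% with the full gain, so the general claim fails.
- **The source of 143 and 72 is a previous publication not reproduced in the protocol.** A reader might infer that the control rate was certainly treated as known. The back-solving makes that plausible, since the two-sample alternatives need base rates far from those cited, but the method is not stated and other inputs cannot be excluded.

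None of this restores 80%. At control rates of 20-40%, no combination tried for 100 versus 91 reaches it, even one-sided with the full biomarker gain.

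**Conclusion.** Wrong as written, and it should be fixed. The AIS paragraph supports n=100 with 80% power for a 10% improvement, and the two-cohort design described in the same section does not deliver that. Two-sided at 5%, for an absolute 10 points and control conversion of 20-40%, power is about 28-35% unadjusted, 38-48% with the gain implied by 100/143 and 50-61% with the full 72/143 gain. The matching detectable differences are about 18-20, 15-17 and 13-14 points.

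The base rate, alpha, sidedness and absolute reading are assumptions, and the biomarker scaling is approximate. The shortfall does not depend on how 143 was derived. It is confined to the AIS justification and is no finding against the power of the motor score endpoint.

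**What to change.** Redo the AIS paragraph of the Sample Size Calculation as a two-cohort calculation with the actual number of CAMPER controls available for the analysis. State the control conversion rate, alpha, sidedness and whether the 10% is absolute. Give power for that difference and the detectable difference at 80% power, both unadjusted and with the assumed biomarker gain. Drop the implied 80% power for 10 points.

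Presenting AIS conversion as an estimated difference with a 95% confidence interval would be a reasonable addition, but is optional.

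The cost is a rewritten paragraph with a less favourable figure. No added patients and no change to procedures are needed.

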## 2. BACKGROUND INFORMATION / STUDY RATIONALE

### 2.1. Hemodynamic Management of Acute SCI

Currently, for patients who present with acute SCI, there are few available treatment options to potentially improve neurologic outcome. One is **early surgical decompression**. In cervical SCI patients, this may afford some degree of neuroprotection and appears to improve neurologic outcome. The second is **aggressive hemodynamic management** by augmenting MAP to 85-90 mmHg during the first week of injury to ensure that the injured spinal cord receives adequate blood supply.

The importance of aggressive hemodynamic management and the potential for improving neurologic recovery after acute SCI through vigilant MAP maintenance has been acknowledged for many years. Clinical practice guidelines and literature reviews recommend the avoidance of hypotension and the maintenance of MAP at 85-90 mmHg for one week post-injury [1-4]. The guidelines themselves, however, acknowledge the lack of strong evidence to support this MAP target. Recent work by Manley and colleagues at the University of California, San Francisco (UCSF) has demonstrated that improved neurologic recovery can be associated with small increases in MAP during the first 3 to 7 days post-injury [5]. By analyzing almost 1 million MAP measurements of acute SCI patients, the UCSF team observed that the difference in MAP between those patients who improved their ASIA Impairment Scale (AIS) grade and those who did not improve was less than 5 mmHg. **This suggests that efforts to improve spinal cord perfusion by even a few mmHg can result in clinically meaningful neurologic improvements for the acute SCI patient.**

Even though clinical practice guidelines do exist (and most specialized trauma centers likely endeavor to adhere to them), the hemodynamic management of an acute SCI patient is not straightforward. Simply deciding upon a MAP target (e.g. 85-90 mmHg) does not necessarily mean that this MAP is actually achieved. Both we and the UCSF group have shown that acute SCI patients frequently experience episodes of significant hypotension, despite being managed in experienced SCI centers ostensibly adhering to the guidelines [5, 6]. Therefore, it is recognized that even in specialized centers, there is room to improve upon the hemodynamic management of acute SCI patients.

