## 5. STUDY PROCEDURES

### 5.1 Enrolment

Spinal cord injured patients will arrive at their respective trauma centers and, after being triaged and stabilized according to standard trauma protocols, the patients will be evaluated by staff (residents or fellows), and a complete neurologic examination will be performed using the International Standards for Neurologic Classification of Spinal Cord Injury (ISNCSCI) examination. The motor-sensory examination will be recorded and the AIS grade will be assigned.

SCI patients will be approached for enrolment in this study ***if the attending spine surgeon has decided that the insertion of a lumbar intrathecal catheter for monitoring ITP and maintaining SCPP is clinically indicated for their hemodynamic management.*** It is important to point out here that the decision to insert the lumbar intrathecal catheter for ITP monitoring and management is a clinical decision made by the surgical team. The rationale for the clinical decision to install a lumbar catheter is derived from our previous publication showing that SCPP is a more meaningful reflection of neurologic recovery than MAP [11]. Centers participating in this study are centers where the spine surgeons have adopted the insertion of the lumbar intrathecal catheter as part of the hemodynamic management of the acute SCI patient. This research protocol will seek to characterize how such active SCPP management influences neurologic outcome.

If the surgeon has decided to insert the intrathecal catheter and actively manage SCPP in the acute SCI patient, the patient will be approached to consider participating in the study. The potential research participant will be informed that the purposes of the study are to 1. evaluate their neurologic recovery over time, 2. obtain CSF and blood samples for biomarker studies, 3. obtain CSF and blood samples for storage in the International Spinal Cord Injury Biobank (ISCIB).

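### The anticipated covariates for the non-randomised comparison with CAMPER include no measure of surgical care, although the protocol treats early decompression as prognostic and takes its 7-point target from it.

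*Protocol*

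**What the plan says.** Section 10 (Efficacy Endpoint) sets the comparison: "Our primary outcome measure will be the change in total motor score at 6 months post-injury", and the "control group will be the prospectively collected (and conventionally managed) cohort from our CAMPER study". The Analysis Plan in the same section specifies multivariable linear and logistic regression: "Anticipated co-variables to control for include AIS grade, neurologic level, baseline motor score", followed by 24-hour post-injury CSF biomarker levels, age and gender. Propensity score matching is the sensitivity analysis; its variables are not listed.

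On decompression the protocol says three things.

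- Section 2.1 names early surgical decompression as one of the few available treatments: "In cervical SCI patients, this may afford some degree of neuroprotection and appears to improve neurologic outcome".
- Section 10 (Sample Size Calculation) proceeds "if we view a 7-point improvement in motor score as both clinically meaningful/achievable", and justifies the 7 points because this effect size "is what appears to be achievable with early surgical decompression in acute SCI".
- Section 2.5 cites a study of acute cervical injury in which AIS A conversion was 43.2% with early and 37.0% with late decompression.

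Section 4.1 allows surgical or non-surgical treatment. On sites, section 2.4 says of CAMPER "This protocol was initiated locally at Vancouver General Hospital, and then expanded to four other hospitals in" London, Halifax, Montreal and San Francisco. Section 5.1 says of CASPER "Centers participating in this study are centers where the spine surgeons have adopted the insertion of the lumbar intrathecal catheter". Section 5.3 names San Francisco and Pittsburgh as examples.

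**The concern.** In a randomised trial, leaving a prognostic factor out of the model costs some precision. Here it can bias the estimate, because nothing but adjustment makes the two cohorts comparable. Section 10 (Study Design Considerations) defends the historical control on exactly this ground, by promising statistical control of confounding.

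The named covariates describe the patient and the severity of the injury. None describes the surgical care received. The protocol nevertheless treats early decompression as beneficial and uses its apparent benefit to size the effect sought. If the cohorts differ in how early, or whether, patients were decompressed, the model as listed leaves some or all of that difference in the coefficient for SCPP management. The error could make an ineffective strategy look effective or hide an effective one.

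**Working it through.** **The plan's own figure.** Inputs from section 10: difference 7, SD 11, α = 0.0499, power 0.806 (printed as β). For two equal groups and a two-sided test,

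n per group = 2 × SD² × (z for α/2 + z for power)² / difference² = 2 × 121 × (1.961 + 0.863)² / 49 = 39.4, so 40 per group and 80 in total.

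The stated figure of about 74 is not reproduced: 37 per group gives power 0.781 (normal approximation) or 0.770 (t distribution). The protocol gives neither sidedness nor allocation against CAMPER. That is a separate matter; 74 is used below only as the planned number of cervical patients.

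**Inputs for the check.**

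- CASPER cervical patients: 74 (section 10). CAMPER cervical patients: 54 (section 2.4).
- SD 11 and two-sided α 0.0499, critical value 1.96.
- Benefit of early decompression in cervical patients: assumed to be the protocol's 7 points.
- Difference between cohorts in the share decompressed early, d: not in the document. Assumed range 0 to 30 percentage points, in either direction.

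**Step 1, standard error.** SE = 11 × √(1/74 + 1/54) = 1.97 points.

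**Step 2, bias.** Bias = 7 × d. Each 10 percentage points contributes 0.7 motor points, one tenth of the effect sought.

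**Step 3, more early decompression in CASPER and no true effect.** Rejection probability = P(Z > 1.96 − bias/SE) + P(Z < −1.96 − bias/SE). For d = 30 points: 2.1/1.97 = 1.07; the upper tail beyond 0.89 is 0.186 and the lower tail 0.001, total 0.187.

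**Step 4, less early decompression in CASPER and a true effect of 7.** Power = Φ((7 − bias)/SE − 1.96). For d = 30 points: 4.9/1.97 − 1.96 = 0.53, so power is 0.70.

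| d (percentage points) | Bias (motor points) | False-positive rate (step 3) | Power (step 4) |
|---|---|---|---|
| 0 | 0 | 0.050 | 0.945 |
| 10 | 0.7 | 0.064 | 0.892 |
| 20 | 1.4 | 0.109 | 0.812 |
| 30 | 2.1 | 0.187 | 0.701 |

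The calculation takes none of the decompression difference as absorbed by the listed covariates and uses the protocol's SD unchanged.

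**The case against.** The strongest reply is that the covariate list is provisional: it is worded as anticipated and as including the named items, and a statistical analysis plan that is not shown could extend it. The propensity variables are unlisted, so they cannot be said to exclude surgical timing. This stands, and it lowers the severity. It does not dispose of the point: the protocol chose to name a set, and that set omits the one co-treatment it uses to size its effect.

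Several stronger readings are tempting, and the document does not support them.

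- A reader might infer that the protocol says early decompression by itself yields 7 points. It says only that this much appears achievable, and section 2.1 is equally hedged and limited to cervical injury. The conversion rates in section 2.5 concern another outcome.
- A reader might infer that CASPER patients were operated on earlier, since section 4.1 requires a blood sample within 24 hours while CAMPER took admissions within 48 hours. Timing of surgery is given for neither cohort, so the direction is open.
- A reader might apply the 7 points to all 100 v 91 patients, which at a 30-point difference would give a false-positive rate of 26%. That extends to thoracic patients a benefit stated for cervical ones, although section 10 says thoracic motor scores are less responsive.
- A reader might say that the whole cohort difference in surgery would be credited to SCPP management. The listed covariates may absorb part of it: timing may correlate with AIS grade and level, and a 24-hour biomarker sample may follow early surgery.
- A reader might infer that surgical times are not collected because the Schedule of Procedures has no row for them. The case report forms are not shown, so this cannot be concluded.

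On site, section 5.3 gives examples only, San Francisco appears in both cohorts, and Vancouver practice is described throughout the CASPER procedures. The overlap may be considerable, and the full CASPER list is unknown.

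**Conclusion.** The point holds as a gap in the named adjustment set: it contains no measure of surgical care, in a comparison that depends on adjustment. The size and direction of any resulting bias are unknown. On the assumption that early decompression is worth 7 points in cervical patients, a 20-percentage-point difference between cohorts roughly doubles the false-positive rate of the cervical comparison, from 5% to 11%, or cuts power for a true 7 points from about 0.95 to 0.81. A 10-point difference does little harm (6%, or power 0.89).

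These figures rest on the assumed range of imbalance, the 7-point benefit, SD 11, 74 v 54 patients and no absorption by other covariates. This should be fixed because the remedy is cheap; the document does not show that the comparison is in fact biased.

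**What to change.** In section 10 (Analysis Plan), add hours from injury to surgical decompression, with a separate category for patients not operated on, to the regression covariates and name it as a variable in the propensity model. State where it comes from in each cohort: the case report form for CASPER, and the study records or hospital chart for CAMPER.

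Add a pre-specified sensitivity analysis restricted to sites that contributed patients to both cohorts. Site adjustment should not be relied on beyond those sites: a site in only one cohort is aliased with treatment, and calendar period is aliased with it entirely, so no covariate can remove that part.

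The cost is a few degrees of freedom, some chart abstraction for CAMPER, and a shared-site analysis that is smaller and less precise. No treatment or procedure changes.
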